###  Interventions

Professional and effective dysphagia management and successful rehabilitation after stroke depend on targeted and standardized imaging diagnostics to assess both symptoms and underlying pathomechanisms. In Germany, FEES has become the most widely used imaging tool for diagnostics of dysphagia [25]. Based on evidence-based dysphagia scores, investigators are able to determine both the severity of dysphagic symptoms and adequate therapy and diet [30–34].

TEE, a semi-invasive procedure, provides enhanced visualization of the heart’s structure and function, particularly for assessing the intra-atrial septum and heart valves, often yielding more detailed results compared to transthoracic echocardiography [16]. Over the past few decades, TEE has become a routine examination in the diagnostic work-up of stroke. While it is generally considered a minimal invasive and safe procedure, complications such as mucosal injuries, bleeding in the upper gastrointestinal tract or aspiration pneumonia can still occur. In relation to swallowing, injuries to the oesophagus, larynx or pharynx as well as the duration of TEE may contribute to dysphagia [21–24].

### Intervention description

#### Equipment and procedures for FEES

The FEES procedure at UKGM utilizes the Rehder/Partner Swallowing Workstation (Hamburg, Germany), equipped with a Karl Storz 3.6-mm HD videoendoscope and camera system. The endoscopic sequences are recorded using a digital picture archiving and communication system (Rehder/Partner), with an image capture rate of 35 frames per second and a resolution of 1021 × 1021 pixels.

#### Pre-procedural preparation

Before the FEES, nasal decongestion is achieved by administering anti-congestive nose drops. Additionally, nasal mucosa and the nostrils are anesthetized using topically applied lidocaine, delivered via cotton swabs.

#### FEES protocol

FEES is conducted according to a standardized examination protocol of the UKGM (Fig. 2). FEES is performed either by a neurologist or a speech and language therapist (SLT) both board certified with the FEES Certificate of the German Society of Neurology. Initially, a preliminary assessment of the patient’s management of saliva is conducted. Subsequently, the patient is instructed to swallow various test boluses (three teaspoons of water; three sips of water; three teaspoons of applesauce; and three morsels of crispbread). 

**Fig. 2 Fig2:**
[figure not shown]
UKGM standardized FEES examination protocol. Abbreviations: FEES = Flexible Endoscopic Evaluation of Swallowing; SSRS = Secretion Severity Rating Scale; PAS = Penetration-Aspiration-Scale; YSv = Yale Pharyngeal Residue Severity Rating Scale for Valleculae; YSps = Yale Pharyngeal Residue Severity Rating Scale for Piriform Sinus; FOIS-G = Functional Oral Intake Scale (German Version)

#### Dysphagia severity assessment via FEES

Dysphagia severity is evaluated using following dysphagia scores:Secretion Severity Rating Scale (SSRS): this 4-point scale assesses the patient’s ability to manage saliva and secretions, which correlates with the risk of aspiration pneumonia. Higher scores on this scale indicate a greater risk of aspiration pneumonia and respectively more severe dysphagic symptoms [32].The Penetration-Aspiration Scale (PAS): This 8-point scale evaluates the extent of penetration and aspiration of saliva, liquids and food. It also describes the patient’s sensory response to penetration or aspiration and their ability to expectorate the penetrated or aspirated material [30]. Higher scores on this scale indicate more severe dysphagic symptoms with PAS-scores 6–8 indicating different severities of aspiration.Yale Pharyngeal Residue Severity Scale (YS): A 5-point scale that measures the severity of residue in the hypopharynx after swallowing saliva, food and liquids [31]. Higher scores on this scale indicate more severe dysphagic symptoms.Functional Oral Intake Scale: Following each FEES assessment, the patient’s ability to orally intake liquids and food is measured by the 7-point Functional Oral Intake Scale (FOIS-G, German version [33]). Lower scores on this scale indicate a deterioration in oral intake ability, with levels 1–3 corresponding to various levels of non-oral feeding and levels 4–7 corresponding to different levels of oral feeding [33, 34].

#### TEE

The Department of Cardiology at the University Medical Centre of the Justus-Liebig-University in Giessen conducts the TEE using a Philips EPIC 7 C ultrasound workstation and Philips Type X7 and X8 probe. For the procedure, anaesthesia is administered either intravenously with propofol or as a combination of intravenous propofol and local pharyngeal anaesthesia using lidocaine spray. Patients are required to refrain oral intake of food and liquids for at least 6 h prior to the TEE. This restriction continues for 30 min and up to 1 h after the TEE to ensure and minimize complications of potential post TEE dysphagia.

#### Criteria for discontinuing or modifying allocated interventions

The criteria for participant dropout include the following: (1) withdrawal of informed consent by the participant or the authorised surrogate; (2) suicidal behaviour during the trial; (3) occurrence of serious adverse events during the trial; (4) withdrawal deemed necessary for safety or effectiveness; (5) poor compliance with the study protocol; (6) significant violations of the trial protocol by the participant; (7) pregnancy during the study; and (8) inability to maintain contact (lost to follow-up).

#### Criteria for terminating FEES examination

FEES is aborted for any tested substance consistency in case of aspiration of saliva with PAS score > 6 or aspiration of liquid, puree or solid boli during the examination with PAS score > 6.

This protocol ensures a systematic approach to the evaluation of dysphagia and helps assess the risk of aspiration and functional swallowing outcomes in patients.

#### Criteria for terminating TEE examination

TEE examination will be terminated in case of overt gastrointestinal bleeding caused by the examination probe, severe hemodynamic and / or respiratory instability of the patient.

#### Strategies to improve adherence to interventions and auditing

The Project Management group consists of the principal investigator (PI), the study coordinator (SC) and specific personell (medical doctors (MDs) and SLTs).

The project will be managed and coordinated under the guidance of the principal investigator (PI). MDs from the Department of Neurology will be assigned to handle subject enrollment and clinical evaluation, whereas testing will be conducted by an MD and an SLT from the Department of Neurology and by an MD from the Department of Cardiology to ensure complication-free trial progress and maintain project quality. Inter-departmental coordination and communication meetings will be overseen by a project coordinator. The PI will oversee review progress, identify implementation issues and develop solutions in a quarterly group meeting. Quality control personnel and data verification personnel will be appointed to the trial team implementing a quality control plan.

The aim of the quality control plan is to align with the technical framework, ensuring adherence to procedures and systems for data collection, entry and database management. After initiation, regular quality and technical auditing reviews will be conducted by the ethics commitee, prompt feedback given and adjustments made to maintain high execution standards.

#### Protocol amendments

Changes made to the protocol that was appraised positively by the ethics committee must be positively reappraised and approved if the changes

are such that they may affect the subjects’ safety;result in further data collection that necessitates changes to the patient information and/or informed consent form;affect the interpretation of the scientific documents upon which the trial is based or the significance of the results of the trial;significantly affect the leadership or conduct of the trial.

In order to ensure most comparable conditions during trial conduct and in the interest of valid statistical analyses, the lead coordinating investigator or any other person involved in the trial conduct may not alter the study conditions agreed upon and set out in this protocol.

Amendments should be made only in exceptional cases. Any amendment must be set out in writing, at the same time giving the reasons, and signed by all parties concerned. The amendment then becomes part of the study protocol.

Amendments which might have an impact on the well-being of the subject (major amendments) such as the use of additional invasive procedures require an additional approval by the ethics commitee. In addition, a further informed consent form must be signed by all trial subjects enrolled in the trial who might be affected by the amendment. In case of substantial changes, new approvals of the leading ethics committee are required before the changes become effective. Minor changes will only be submitted to the ethics committee in a written form.

#### Relevant concomitant care permitted or prohibited during the trial

Any pharmacological treatment that contradicts the acute treatment of stroke is prohibited. SLT interventions (diagnostic and therapeutic) that ensure an aspiration free dysphagia management are possible during the trial period. At the conclusion of the trial, participants requiring additional treatment of dysphagia will be supported in securing appropriate follow-up care in an outpatient setting or a rehabilitation facility.

## Outcomes

### Primary outcome

The primary outcome will assess the impact of the type and form of anaesthesia (intravenous vs. local) administered during TEE on swallowing in patients with ischaemic stroke and TIA, based on the aforementioned dysphagia scores [30–34].

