### Objectives

Building on the results of the initial TEDRAS trial, this follow-up trial is designed to address the limitations of the first TEDRAS study that were not sufficiently explored: The impact of the duration of TEE on swallowing, the type on anaesthesia as well as the interrater reliability for FEES. In the follow-up TEDRAS trial we will be focusing on patients with ischaemic stroke and transient ischemic attack (TIA) specifically analyzing the following parameters in both groups:The impact of the type and method of anaesthesia administration (intravenous vs. local anesthetic spray application) during TEE on swallowing function in both cohorts.The effect of the duration of the TEE procedure on swallowing function in both cohorts.The experience level of the TEE examiner.The interrater reliability of FEES.

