### Sample size estimation

Given the lack of existing data on the influence of anaesthesia type and form during TEE on swallowing in ischaemic stroke and TIA patients, this study is designed as a pilot trial. A total of 50 participants will be enrolled, with 25 patients in each group (stroke vs. TIA). The primary aim of this exploratory phase is to gather preliminary data to estimate effect sizes. These estimates will then serve as the basis for a formal power calculation and definitive sample size planning for a subsequent full-scale study.

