### Assignment of interventions: allocation

Since this is not a randomized trial the participants will be assigned to the aforementioned groups according to the diagnosis. The allocation sequence will be sequentially numbered by the allocating investigator MD and stored in a secure database only accessible by this person. The trial investigator responsible for enrollment and allocation will provide patients’s enrollment sequence number and allocate participants to respective groups after viewing the diagnosis. All enrolled patients will receive the same interventions in both groups.

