### Statistical methods

Patient-related data such as age, gender, diagnosis, relevant medication, TEE duration and application form of anaesthesia (local or intravenous) are evaluated descriptively with frequency data, mean values with standard deviations or medians with interquartile ranges.

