### Definition of dysphagia

Dysphagia is determined with the following cut-off values of the dysphagia scores:

Secretion Severity Rating Scale for Saliva Management (SSRS): SSRS ≥ 1; Penetration Aspiration Scale (PAS): PAS ≥ 3; Yale Pharyngeal Residue Severity Rating Scale: YS ≥ 3; Functional Oral Intake Scale (FOIS-G): FOIS-G < 7. Differences in patient-related data between the two groups: dysphagia/non-dysphagia group and intravenous vs. oral anaesthesia group are tested using Pearson’s chi-square test, Fischer’s exact test, *t*-test for independent samples or the Mann–Whitney *U*-test. For the purpose of logistic regression analyses, we intend to apply a median split to dichotomize the SSRS, PAS, YS and FOIS-G scores and create a binary outcome variable.

Assumptions for a *t*-test for independent samples are tested with the Levent test for variance homogeneity and the Shapiro–Wilk test including visual inspection of thedistribution plots for the assessment of normal distribution. If there is no homogeneity of variance or normal distribution, the Mann–Whitney *U* test for group differences is used. Correlations are calculated using the Pearson product-moment correlation or the Spearman rank correlation.

The inter-rater reliability between two raters is determined using a linearly weighted Cohen’s kappa, as this takes into account matches that could have arisen by chance on the one hand and places more weight on high non-matches on the other [39]. Furthermore, the percentage agreement and the Spearman rank correlation are specified for the agreement between two raters. In the case of a calculation of inter-rater reliability with more than two raters, a general agreement of all raters including subtraction of agreements by chance is calculated using Fleiss kappa [39].

Effect sizes are given according to Cohen’s d with a 95% confidence interval. *p*-values are given for all statistical results. The criterion for statistical significance is set at *p* < 0.05. Conclusions about clinically, practically and scientifically relevant correlations or differences are not made solely on the basis of the defined statistical significance [40].

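### The primary contrast is intravenous versus local anaesthesia, but both regimens described for TEE contain intravenous propofol, so only the added effect of the spray can be estimated

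*Protocol article*

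**What the plan says.** The primary question is given in the Primary outcome section: "The primary outcome will assess the impact of the type and form of anaesthesia (intravenous vs. local) administered during TEE on swallowing". The Objectives section puts it as "intravenous vs. local anesthetic spray application) during TEE on swallowing function in both cohorts", and the Abstract and the Administrative information table use the same contrast.

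The TEE section, under Intervention description, says what is given: "anaesthesia is administered either intravenously with propofol or as a combination of intravenous propofol and local pharyngeal anaesthesia using lidocaine spray".

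The analysis text names the exposure in two further ways. Statistical methods lists "application form of anaesthesia (local or intravenous" as the two values of the variable. Definition of dysphagia says that differences between an "intravenous vs. oral anaesthesia group are tested using Pearson" and other two-sample tests.

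Anaesthesia is not allocated by the study. Patients are grouped by diagnosis: "Since this is not a randomized trial the participants will be assigned to the aforementioned groups according to the diagnosis". On size: "A total of 50 participants will be enrolled, with 25 patients in each group (stroke vs. TIA". The number expected on each anaesthesia regimen is not given.

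**The concern.** The primary outcome sets two routes of anaesthesia against each other as alternatives. The TEE section describes one agent that everybody receives and a second that some receive in addition. These are different questions. The first asks whether sedation or local anaesthesia is worse for swallowing. The second asks whether numbing the pharynx makes swallowing worse in patients who are already sedated.

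Two things are at stake. A reader of a result labelled intravenous versus local could conclude that one route is safer and could replace the other, for example that spray could stand in for sedation. No patient in the study would have been treated that way. In addition, Sample size estimation says that the pilot's effect-size estimates will be the basis for powering a full-scale study, so an estimate attached to the wrong contrast would carry over into that design.

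**Working it through.** No sample-size or power figure bears on this point. The check compares the regimens described with the contrast stated.

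**Inputs**

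- Regimens: propofol alone, or propofol plus lidocaine spray (TEE section).
- Stated contrast: intravenous versus local (Primary outcome), with spray named as the local form (Abstract, Administrative information, Objectives).
- Coding: local or intravenous (Statistical methods); intravenous or oral (Definition of dysphagia).
- Patients: 25 stroke + 25 TIA = 50 (Sample size estimation).

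**Step 1: who receives what.** Let *s* be the unknown number of patients given spray.

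| Regimen | Propofol | Spray | Patients |
|---|---|---|---|
| Propofol alone | yes | no | 50 − *s* |
| Propofol plus spray | yes | yes | *s* |
| Spray alone | no | yes | 0 |

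Propofol is given to (50 − *s*) + *s* = 50 of 50 patients. Local anaesthesia alone is given to 0 of 50. The lidocaine in Pre-procedural preparation is applied to the nose before FEES. It is not TEE anaesthesia and does not create a local-only group.

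**Step 2: what the labels do with these patients.**

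| Reading of the two labels | Intravenous | Local |
|---|---|---|
| Each label means that agent only | 50 − *s* | 0; the *s* combined patients have no category |
| Each label means that agent was given at all | 50 | *s*, all of them also counted as intravenous |
| Local is shorthand for propofol plus spray | 50 − *s* | *s* |

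Only the third reading yields two exclusive groups that cover everyone, and the protocol does not state it.

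**Step 3: what can be estimated.** Write the mean swallowing score after TEE as *a* + *bP* + *cL*, where *P* = 1 if propofol was given, *L* = 1 if spray was given, and *a* includes the effect of TEE itself.

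- Contrast as stated, intravenous only minus local only: (*a* + *b*) − (*a* + *c*) = *b* − *c*.
- Contrast available, propofol plus spray minus propofol alone: (*a* + *b* + *c*) − (*a* + *b*) = *c*.

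Since *P* = 1 for everyone, *a* and *b* enter only as the sum *a* + *b*. The propofol effect *b* cannot be separated from the effect of TEE, so *b* − *c* is not identified at any sample size. For example, if the spray has no effect (*c* = 0), the two groups will look alike on average. A report under the present label would say that intravenous and local anaesthesia are equivalent for swallowing, although *b* could take any value.

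**The case against.** The strongest reply is that *local* is shorthand for the regimen that includes the local agent. The TEE section offers its two regimens as alternatives, so each patient falls into exactly one, neither group is empty by definition, and a two-group comparison is feasible. *Oral* is then a slip for the pharyngeal spray, and the remedy is rewording. The study is also an exploratory pilot, and the protocol says that conclusions will not rest on significance alone.

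Much of this is fair. The two regimens are mutually exclusive; the overlap lies in the labels. *Oral* is probably a slip, because no oral anaesthetic is described anywhere. The TEE section is also a short account of departmental practice and could have left out a spray-only option. The counts of 50 and 0 are therefore inferences from that section, not figures the protocol reports.

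The reply does not remove the problem. Reading *local* as propofol plus spray concedes that the question the data can answer is an add-on question, which differs from the one written as primary. Pilot status does not excuse this, since producing an effect size for the next study is the pilot's declared purpose. Nor is it a detail that a condensed article may leave to a fuller document: the article makes incompatible statements about its own primary exposure, and nothing in it reconciles them.

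**Conclusion.** The point holds, and it must be fixed because it concerns the primary outcome. If the TEE section is accurate, 50 of 50 patients receive intravenous propofol, 0 of 50 receive local anaesthesia alone, and the stated contrast cannot be estimated. What can be estimated is the difference between propofol plus spray and propofol alone. Because anaesthesia is not randomised, that difference remains an observational comparison even when correctly named.

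The conclusion rests on one assumption, that no patient has TEE under spray alone. If some do, the TEE section is wrong instead, and the exposure has three levels where the analysis provides two. The text needs correcting in either case.

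**What to change.** The sponsor should first confirm with the cardiology department which regimens are used.

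- **If the TEE section is correct:** restate the primary contrast as propofol plus lidocaine spray versus propofol alone. Use that one label in the Abstract, Administrative information, Objectives, Primary outcome, Statistical methods and Definition of dysphagia, and drop *oral*. Limit the conclusion to the additional effect of the spray in patients sedated with propofol.
- **If spray-only TEE also occurs:** correct the TEE section, define three exclusive categories (propofol alone, propofol plus spray, spray alone), and say which pair forms the primary contrast.

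In both cases, derive the category from the agents recorded for each patient.

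The cost is rewording the objective, the primary outcome and one analysis variable, and submitting the change to the ethics board as the protocol requires for modifications. The form of anaesthesia is already among the data to be collected, so no further patients or procedures are needed, provided the agents given are noted. The price is a narrower claim.

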### Secondary outcomes

Comparison of TEE duration between patients with and without dysphagia and in cases of ischaemic stroke and TIA;Correlation between TEE duration and the degree of deterioration in FOIS-G and the experience of the TEE examiner in patients with ischaemic stroke and TIA;Correlation between TEE duration and TEE examiner’s experience in patients with ischaemic stroke and TIA;Interrater reliability in the evaluation of FEES.

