## Discussion

This protocol presents a pilot prospective single-blinded controlled study designed to assess further risks of dysphagia following TEE. The trial aims to address several outcomes which will be correlated with the severity of dysphagia after TEE, building on the findings from the initial trial.

The initial TEDRAS study revealed a notable increase in all dysphagia outcome scores in the intervention group immediately following TEE, alongside a significant increase in residue scores for all consistencies in the valleculae, and for small and large liquid boluses in the piriform sinus. These findings align with Grimm et al. [41], who identified residue as the most common dysphagia symptom in patients post-intraoperative TEE. Additionally, a prospective randomized trial by Chin et al. [24] confirmed that prolonged intraoperative TEE placement in the esophagus negatively impacts swallowing in cardiac patients. However, the initial TEDRAS trial did not evaluate the effect of TEE duration on swallowing. Based on the TEE probe’s diameter, weight and the anatomical proportions of the human oral cavity and tongue, it was hypothesized in the initial trial that the probe exerts excessive pressure on the oral, pharyngeal and laryngeal tissues, impairing the motility of the tongue, tongue base, pharyngeal wall, larynx and upper esophageal sphincter. Lastly, the initial TEDRAS study did not investigate the influence of anaesthesia on swallowing. The aim of the TEDRAS 2 follow-pp study is to address the above-mentioned limitations of the initial TEDRAS study in order to determine which factors are leading to dysphagic symptoms after TEE and thus to ensure a good aspiration prevention for stroke patients undergoing TEE.

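### The stated analyses of TEE duration are unadjusted, so they cannot isolate the duration effect named in the objectives if examiner experience, anaesthesia form or diagnosis is linked to both duration and swallowing

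*Protocol article*

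**What the plan says.** The Objectives section of the protocol article lists "The effect of the duration of the TEE procedure on swallowing function in both cohorts". The Discussion says that the study should address the first trial's gaps "in order to determine which factors are leading to dysphagic symptoms after TEE".

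Secondary outcomes gives two analyses that bear on duration and swallowing. One compares duration between patients with and without dysphagia. The other is "Correlation between TEE duration and the degree of deterioration in FOIS-G and the experience of the TEE examiner". A further item is "Correlation between TEE duration and TEE examiner’s experience in patients with ischaemic stroke and TIA".

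The methods stand under Definition of dysphagia. For correlations: "Correlations are calculated using the Pearson product-moment correlation or the Spearman rank correlation". For group differences: chi-square, Fisher, t or Mann–Whitney tests. None of these takes a covariate. The same section adds "For the purpose of logistic regression analyses, we intend to apply a median split to dichotomize the SSRS, PAS, YS and FOIS-G scores", but it names no predictors and does not mention duration there.

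Anaesthesia is the main exposure: "The primary outcome will assess the impact of the type and form of anaesthesia (intravenous vs. local) administered during TEE on swallowing". The section on allocation says that the trial is not randomised and that patients are grouped by diagnosis. The TEE section describes two forms of anaesthesia but no rule by which the trial assigns them.

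**The concern.** The aim is worded as an effect, and the Discussion wants to tell contributing factors apart. A two-variable correlation can show that longer examinations go with more deterioration. It cannot show whether duration is responsible or something that travels with it.

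Three recorded factors could play that part:

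- **Examiner experience.** Its correlation with duration is a secondary outcome, and the Objectives list it as a parameter beside duration.
- **Anaesthesia form.** Its influence on swallowing is the primary question.
- **Diagnosis.** Duration is to be looked at in stroke and in TIA, and the Background puts dysphagia at no less than half of stroke patients.

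The protocol treats these links as open enough to study, yet does not carry them into the duration analysis. The pilot is meant to supply effect sizes. Confounding shifts the estimate itself, so the protocol's sensible caution about p-values does not remove it. The shift can go either way: links of opposite sign can hide a real effect.

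**Working it through.** The protocol gives no power, effect size or formula for the duration analysis, so there is no figure to reproduce. The check asks how often the unadjusted test would declare a duration effect when there is none.

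**Inputs from the protocol article**

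- n = 50, with 25 stroke and 25 TIA (Sample size estimation).
- Significance at p < 0.05 (Definition of dysphagia). Sidedness is not stated; two-sided is assumed.
- FOIS-G is a 7-point ordinal scale (Dysphagia severity assessment via FEES).

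**Assumed inputs, not in the protocol**

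- a = correlation of the third factor C with duration; b = correlation of C with FOIS-G deterioration. Both are varied from 0 to 0.7.
- For the ordinal version, a four-level deterioration score with 60% of patients showing none.

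**Step 1: the spurious correlation.** If duration D has no path to the outcome Y and both depend on C, then corr(D, Y) = a × b. For 0.3 and 0.3 this is 0.09; for 0.5 and 0.5 it is 0.25.

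**Step 2: rejection rate of the unadjusted test, by Fisher z.** m = atanh(ab) × √(n − 3), and the rate is Φ(m − 1.96) + Φ(−m − 1.96).

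- a = b = 0.3: m = 0.0902 × √47 = 0.62; rate = Φ(−1.34) + Φ(−2.58) = 0.095.
- a = b = 0.5: m = 0.2554 × √47 = 1.75; rate = Φ(−0.21) + Φ(−3.71) = 0.417.

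**Step 3: simulation, 10,000 trials per setting, true duration effect zero.**

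| n | a | b | Unadjusted Pearson | Unadjusted Spearman, ordinal score |
|---|---|---|---|---|
| 50 | 0 | 0 | 4.8% | 4.6% |
| 50 | 0.5 | 0 | 5.2% | 4.7% |
| 50 | 0.3 | 0.3 | 9.4% | 8.6% |
| 50 | 0.4 | 0.4 | 20.1% | 15.0% |
| 50 | 0.5 | 0.5 | 42.9% | 29.6% |
| 50 | 0.7 | 0.7 | 96.0% | 84.8% |
| 25 | 0.3 | 0.3 | 6.8% | 6.7% |
| 25 | 0.5 | 0.5 | 23.0% | 16.1% |

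The Pearson column agrees with the Fisher z values in step 2.

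**Step 4: the same data with adjustment.** The partial correlation is (r_DY − r_DC × r_YC) / √[(1 − r_DC²)(1 − r_YC²)]. With r_DY = ab, r_DC = a and r_YC = b, the numerator is ab − ab = 0. In the simulations its rejection rate was 4.6% to 5.7% in every setting, for n = 50 and n = 25.

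**Step 5: the condition.** The row with a = 0.5 and b = 0 shows that a link between C and duration is not enough. C must also reach swallowing by a route other than duration.

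**The case against.** The strongest reply has four parts.

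*A multivariable model is mentioned.* Logistic regression on the dichotomised scores is planned, and predictor lists are often left to a fuller document. This stands to the extent that a reader who infers that no multivariable analysis is planned goes beyond the text. It does not settle the point, because the regression is not tied to duration, whereas the correlation and the group comparison are.

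*The quoted outcome names three variables.* Since duration against experience is listed separately, the item could mean a joint analysis. The wording allows this, but the only correlation methods given are Pearson and Spearman, which take two variables at a time.

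*Diagnosis may be handled by separate analyses.* The phrases about both cohorts can be read as cohort-wise analysis. That would remove confounding by diagnosis and reduce n to 25, where the inflation is smaller. Experience and anaesthesia form would remain.

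*The links are not established.* This stands. A reader might infer that duration depends on examiner experience; the protocol only plans to examine that. It states no link between duration and anaesthesia form at all. If experience affects swallowing only through duration, there is no spurious effect.

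It is also fair to say that this is a secondary outcome of an exploratory pilot, that conclusions are not to rest on significance alone, and that the duration correlation is not singled out as the basis for sizing the later study.

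**Conclusion.** The point holds as a mismatch between aim and method. The aim is the effect of duration among several candidate factors. The analyses tied to it are unadjusted, in a study where duration, examiner and anaesthesia form are not described as assigned by the trial.

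The size cannot be known from the protocol. At n = 50 with no true effect, the false-positive rate is about 9% for assumed links of 0.3 and 0.3, and about 30% (ordinal Spearman) to 43% (Pearson) for 0.5 and 0.5, against about 5% after adjustment. These rates rest wholly on the assumed correlations and on the factor having its own route to swallowing. They should not be read as a forecast for this trial: the documents give no values for either link. What they do show is that the stated analysis cannot tell the two situations apart, while an inexpensive alternative can.

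**What to change.** In Secondary outcomes and in the statistical methods, state that the duration effect is estimated by a partial Spearman correlation of TEE duration with FOIS-G change, adjusting for examiner experience, anaesthesia form and diagnosis, with a 95% confidence interval. A parsimonious linear model of post-TEE FOIS-G on FEES 1 FOIS-G, duration and the same three terms is an alternative. Name the post-TEE examination used. Report the bivariate correlations and the two-group comparison of duration as descriptive associations, not as effects of duration.

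No new data are needed. Duration, anaesthesia form and diagnosis are among the variables listed under Statistical methods, experience is already required by the secondary outcomes, and FOIS-G is scored after each FEES.

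The cost is modest. With one term per factor, residual degrees of freedom fall from 50 − 2 = 48 to 48 − 3 = 45, and intervals widen somewhat. Estimates may be unstable if few patients deteriorate. For that reason the partial rank correlation is safer here than an ordinal model with five predictors.
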